**Phase III: Assessment of mobile app usability**

Phase III will involve the release of a Beta version (completion of the app’s development) [51] once corrections of the Alpha version are completed. The Beta version testing will be conducted on eligible participants to inform the app’s usability [52]. This phase will take approximately three months. The researcher will provide continuous feedback to the mobile app developer, and regular meetings will be held until a consensus is reached. Findings from Phase III will be used to provide input to the mobile app developer for modifications before the final prototype is released. 

**Study setting**

Phase III will be conducted at the Geriatric Department of UMMC and the Memory Clinic of GHKL. The estimated time frame is approximately three months.

**Study population and sampling procedure**

The target population in this phase is PLwD caregivers. We will recruit caregivers of PLwD who attend regular follow-ups at UMMC and GHKL. Prior to recruitment, the researcher will contact the healthcare staff at the selected institutions to estimate the total number of patients and their caregivers. If the amount is large enough to allow random sampling, this method will be done to select respondents. However, convenient sampling may be employed if the number is too small to allow for adequate probability sampling. The inclusion and exclusion criteria for caregivers are presented in Table 2.

**Sample size calculation**

The sample-to-item ratio of 5:1 will be used [53]. Since the M-MAUQ scale consists of 18 items, a total of 90 participants will be needed. Previous similar studies have also shown a comparable sample size [32,54,55]. With a potential non-response rate of 20%, approximately 108 individuals will be invited to join the study.

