**Variables and tools**

The usability of a mobile app is defined as the quality attribute that assesses how easy a system interface is for users [56]. Usability generally includes three domains: ease of use, interface and satisfaction, and usefulness. The *ease of use* domain in this study is defined as the extent to which understanding, learning, and operating the mobile app’s specific system or technology is free of physical and mental effort [57,58]. The *interface and user satisfaction* are linked to the convenience of obtaining quality information through the mobile app [59]. Lastly, *usefulness* is defined as the quality of having utility (helpfulness of the mobile app) in serving the intended purpose [60]. 

Usability is measured using the M-MAUQ scale [61]. The mHealth App Usability Questionnaire (MAUQ) was originally developed by Zhou and colleagues to evaluate the usability of mobile health applications among patients and healthcare providers [62]. It came in four versions that assess the type of app (interactive or standalone) and intended audience (patient or health care provider). For this study, the phrase “MAUQ standalone used by patient” is used. The term “patient” here refers to an individual who utilizes a mHealth application to monitor, improve, or manage their health [61,62]. According to Zhou, the questionnaire comprises 18 items and is divided into three subscales: ease of use (five items), interface and satisfaction (seven items), and usefulness (six items). Participants rate each item on a seven-point Likert scale ranging from 1 (strongly disagree) to 7 (strongly agree). App usability is determined by the sum and average of all statements—the higher the average, the better. However, if the average score is less than 4, the app’s usability is poor [61]. The highest possible score is 126, and the lowest is 18. An average score equal to, or greater than 72 indicates that the app is usable. The M-MAUQ questionnaire has been translated into the Malay language and validated among the Malaysian population with a Cronbach alpha of 0.94 [61]. Its content validity indexes (CVI) for relevance and clarity were 0.98 and 0.94, respectively, and the face validity index for understandability was 0.96. For each item in M-MAUQ, the kappa statistic indicated high agreement between raters, ranging from 0.76 to 1.09 [61]. 

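### Minor arithmetic correction: 108 invitations are 90 × 1.2, not 90 ÷ 0.80, so at 20% non-response they are expected to yield about 86 respondents rather than 90

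*Protocol article*

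**What the plan says.** The section on sample size calculation (Protocol article, Methodology, Phase III) sizes the usability survey by a rule of five participants per questionnaire item: "Since the M-MAUQ scale consists of 18 items, a total of 90 participants will be needed". It adds that similar earlier studies were of comparable size. It then allows for loss: "With a potential non-response rate of 20%, approximately 108 individuals will be invited to join the study".

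The section on variables and tools confirms the item count through the three subscales, of five, seven and six items. The formula behind the 108 is not shown. The article gives no other invitation number and no rule for replacing or topping up non-respondents.

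**The concern.** The allowance sentence exists to protect the target of 90. A non-response rate has the people invited as its denominator, so the number to invite is the target divided by the proportion expected to respond. Adding 20% of the target to the target is a different operation and always gives too few. The stated need, the stated rate and the stated number of invitations therefore contradict one another within one short paragraph.

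What is at stake is whether the plan, under its own assumption, meets its own target and its own 5:1 ratio. That ratio is the main basis given for the size of Phase III.

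**Working it through.** **Inputs** (all from the sample size section; the item count is also in the section on variables and tools)

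- Ratio: 5 participants per item
- Items: 5 + 7 + 6 = 18
- Target: 90
- Non-response rate: 20%
- Invitations: about 108

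**Step 1. Reproduce the plan's figures.**

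- Target: 18 × 5 = 90, as stated.
- Invitations: 90 × (1 + 0.20) = 108, exactly as stated. This is evidently how the figure was obtained.

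**Step 2. Apply the stated rate to the stated invitations.**

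- Expected respondents: 108 × (1 − 0.20) = 86.4, about 86.
- Shortfall: 90 − 86.4 = 3.6, about 4.
- Ratio: 86.4 / 18 = 4.8 per item, against 5.

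**Step 3. Find the number of invitations that fits the target and the rate.**

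- 90 / (1 − 0.20) = 112.5, rounded up to 113.
- Check: 113 × 0.80 = 90.4, which meets 90.
- Difference from the plan: 113 − 108 = 5 invitations, or 5/108 = 4.6%.

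**Step 4. Find the rate that fits the target and the 108.**

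- 1 − 90/108 = 0.167. So 108 invitations yield 90 only if non-response is no more than about 16.7%.

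**Step 5. Size of the effect.**

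- Precision: the standard error of a mean scales with 1/√n. The inflation is √(90/86.4) = 1.02, about 2%.
- Chance of reaching the target: if each invitee responds independently with probability 0.80 (an assumption that is not in the article), the probability of at least 90 respondents is about 23% with 108 invited and about 59% with 113. The finding does not depend on this step.

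**The case against.** Several things can be said for the plan.

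- **The article gives the invitation number only as an approximation.** This does not close the gap. 108 is the exact product 90 × 1.2, not a rounding of 112.5.
- **The 20% may have been meant as a margin on top of 90.** The text calls it a non-response rate and ties it to those invited. On that meaning, 108 and 90 together imply about 16.7%, not 20%.
- **The number invited may not bind.** The section on study population and sampling leaves the choice between random and convenience sampling to how many caregivers are found, and the Discussion mentions universal sampling as a possibility. Under universal sampling the available population would set the count. This stands as a reason not to say that the study is bound to fall short. It does not correct the printed figure.
- **The consequence is slight.** This stands in full. The 90 comes from a rule of thumb, not from a power or precision calculation. The planned Phase III analysis reports means and standard deviations of the total and domain scores against fixed cut-offs. The article describes no hypothesis test, group comparison or factor analysis whose validity rests on a ratio of exactly 5:1.

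A reader might also infer that the 20% has to absorb refusal, failure to download the app, and drop-out over the four to six weeks of use, and that the article should say so. The documents do not support this as a finding. The article does not define the stages that its rate covers, and a condensed article may leave that definition to the full protocol.

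**Conclusion.** The invitation figure is wrong as written. At the stated 20% non-response, "approximately 108 individuals will be invited to join the study" gives an expected 86 or so respondents (4.8 per item), while the same paragraph says that "a total of 90 participants will be needed" (5 per item). The contradiction follows from the article's own numbers and needs no outside assumption.

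The replacement figure of 113 does rest on one assumption: that the 20% is a single overall loss from those invited. If losses arise at several stages and together exceed 20%, 113 would not be assured of yielding 90 either.

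This is a minor correction. A reader might infer that Phase III would be too small to support its conclusions. The documents do not support that: about four fewer respondents add about 2% to the standard error of a mean, and no stated conclusion depends on it.

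**What to change.** Make the target, the rate and the number of invitations agree. Any one of these does so:

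1. **Change the invitations.** Taking 20% as one overall loss from those invited, replace 108 with 113 (90/0.80 = 112.5, rounded up). The cost is five more invitations.
2. **Change the expected yield.** Keep 108 and the 20%, and restate the expected number of respondents as about 86. The ratio must then be restated too, as about 4.8:1; otherwise the 5:1 statement remains unmet.
3. **Change the allowance.** Keep 108 and 90, and restate the non-response allowance as about 16.7%. This costs only wording, but it makes sense only if the authors consider that rate realistic.

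Option 1 is the simplest: it changes one number and leaves the 90, the 5:1 ratio and the 20% as they are. None of the options touches the analysis.

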**Data collection**

After obtaining verbal and written consent from each respondent, the researcher will instruct participants to download the mobile app into their smartphones. Respondents are given four to six weeks to test and use the mobile app. Subsequently, the researcher will administer an online questionnaire via e-mail or WhatsApp containing the usability scale for assessment. 

**Variables and tools**

The usability of a mobile app is defined as the quality attribute that assesses how easy a system interface is for users [56]. Usability generally includes three domains: ease of use, interface and satisfaction, and usefulness. The *ease of use* domain in this study is defined as the extent to which understanding, learning, and operating the mobile app’s specific system or technology is free of physical and mental effort [57,58]. The *interface and user satisfaction* are linked to the convenience of obtaining quality information through the mobile app [59]. Lastly, *usefulness* is defined as the quality of having utility (helpfulness of the mobile app) in serving the intended purpose [60]. 

Usability is measured using the M-MAUQ scale [61]. The mHealth App Usability Questionnaire (MAUQ) was originally developed by Zhou and colleagues to evaluate the usability of mobile health applications among patients and healthcare providers [62]. It came in four versions that assess the type of app (interactive or standalone) and intended audience (patient or health care provider). For this study, the phrase “MAUQ standalone used by patient” is used. The term “patient” here refers to an individual who utilizes a mHealth application to monitor, improve, or manage their health [61,62]. According to Zhou, the questionnaire comprises 18 items and is divided into three subscales: ease of use (five items), interface and satisfaction (seven items), and usefulness (six items). Participants rate each item on a seven-point Likert scale ranging from 1 (strongly disagree) to 7 (strongly agree). App usability is determined by the sum and average of all statements—the higher the average, the better. However, if the average score is less than 4, the app’s usability is poor [61]. The highest possible score is 126, and the lowest is 18. An average score equal to, or greater than 72 indicates that the app is usable. The M-MAUQ questionnaire has been translated into the Malay language and validated among the Malaysian population with a Cronbach alpha of 0.94 [61]. Its content validity indexes (CVI) for relevance and clarity were 0.98 and 0.94, respectively, and the face validity index for understandability was 0.96. For each item in M-MAUQ, the kappa statistic indicated high agreement between raters, ranging from 0.76 to 1.09 [61]. 

For further clarification, we provide the operational definition and scoring system of the variables of interest in Phase III (usability) and its domains. Table 3 (below) shows the operational definition of usability and its domains.

**Methods of data management**

Phase I data management will follow the guidelines recommended by Knight (2018) for interviews and FGDs [63]. First, a digital voice recorder will be used to record the entire session if the session is conducted on-site. Meanwhile, if the session is virtual, a screen or meeting recording with encryption in the platform will be used. Next, the audio recordings and other data collected will be labeled with the date, location, and name of the participant and kept by the researcher for analysis. Finally, all participants will be informed about how the data are collected, managed, and used.

In Phase III, data from the Google form will be transferred into an Excel file (Version 2202), which is used for data cleaning and coding. We expect and aim for no missing data, and this is ensured by configuring the Google form’s settings to mandate participants to answer all questions. Data will be verified before importing into the IBM Statistical Package for Social Sciences (SPSS) software version 26.0 for analyses. 

All data will be password protected and accessible only to the main researcher(s). They will also remain anonymous, and confidentiality will be ensured. Upon completion of the study, the Google form link will be disabled, and no other person except for the researchers will be able to access the information. All data in the Google cloud storage will be deleted or inactivated five years from the final publication date [64].

**Ethics Approval**

This study has been approved by the Malaysian Research and Ethics Committee (MREC), which serves as the principal National Medical Research Registry (NMRR) in Malaysia, Registration ID-22-00546-EBB (IIR) and the institute; University Teknologi MARA (UiTM) (Reference number: REC/07/2022 PG/MR/153). The study will be conducted in accordance with National Institutes of Health (NIH) standards [65]. Any modifications to the procedures stated in this protocol will be forwarded to the Malaysian Research and Ethics Committee (MREC), which serves as the principal National Medical Research Registry (NMRR) in Malaysia and explained in subsequent publications. 

The overall flow of the study is demonstrated in Figure 1 below. A continuous literature review will be conducted to stay on track and be informed about the most recent information available.

## 3. Expected Results

**i.** 
**Phase I:**

Even though the final content will be determined based on the FGD with the experts and NGT with dementia caregivers, we expect several topics or themes to emerge from the discussions [38]. Examples are not restricted to but may include:

(a)Educational materials in a written form (i.e., behavioral, and psychological symptoms, pharmaceutical side effects, nutritional and oral health, and disease progression or complications).(b)Effective communication abilities (communication strategies or sharing experiences with other caregivers)(c)Reminders (e.g., medication diary and appointment with a physician for PLwD)(d)Psycho-spiritual assistance (e.g., a list of prayers or motivational quotes that are suited to the Malaysian cultural and religious ethos.)(e)Access to nearby healthcare facilities or local community resources (a directory of hospitals, geriatric units, dementia centers, non-governmental organizations, police, and fire stations)

The scores from FGD will be presented in mean and standard deviation, and results will be determined according to the NGT threshold [45]. FGD results will be guided by thematic analyses [66].

**ii.** 
**Phase II:**

An offline mobile app prototype called “Demensia KITA” in *Bahasa Malaysia* is user-friendly, culturally appropriate for local PLwD caregivers, and available in the Android Google Play Store, free of charge. 

**iii.** 
**Phase III:**

**Mobile app usability**

The total mean scores for usability from the M-MAUQ will be calculated and expressed as mean and standard deviation (SD) and tabulated. A total mean score equal to, or more than, 72 indicates that the app has good usability and vice versa. The mean score of each domain in the M-MAUQ (i.e., ease of use, usefulness, interface, and satisfaction) will be calculated. A cut-off score of ≥4 from each item in the domain indicates good usability. 

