## Figures and Tables

**Figure 1 ijerph-19-11880-f001:**
[figure not shown]
Overall study flowchart.

**Table 1 ijerph-19-11880-t001:** Example of Nominal Group Technique Voting Scores Template.

Solution/Ideas	Participant 1	Participant 2	Participant 3	Participant 4	Participant 5	NGT Scores
Solution/Idea 1	4	4	5	4	5	22
Solution/Idea 2	2	1	3	2	2	10
Solution/Idea 3	5	5	5	4	4	23
Solution/Idea 4	3	1	5	2	4	15
Solution/Idea 5	4	4	5	4	3	20

**Table 2 ijerph-19-11880-t002:** Inclusion and exclusion criteria in Phase III.

Criteria	Eligibility
**Inclusion**	Primary caregiver of a person living with dementia. A primary caregiver in this study is defined as a person who helps in the personal care of an older adult with dementia, regardless of their education or experience for one month or more during the last 12 months [43,44]. Aged ≥ 18 years old. Caring for an older relative aged ≥ 60 years old diagnosed with any form of dementia. Owns a working and compatible smartphone (Android with mobile data). Has basic knowledge of using smartphones and apps.
**Exclusion**	Not able to communicate independently in English or Bahasa Malaysia. Does not use Android as their mobile operating system.

**Table 3 ijerph-19-11880-t003:** Operational definition of usability and its domains.

Variable/Domain	Operational Definition
**Usability of mobile app**	Usability is determined by the total and mean scores of all domains (ease of use, interface, and usefulness) derived from the M-MAUQ. Higher scores indicate greater usability. A total mean score equal to, or more than, 72 denotes that the app has good usability and vice versa.
**(a) Ease of use**	There are 5 items under this domain. A total mean score equal to, or more than, 20 under indicates that the app is easy to use, and vice versa.
**(b) Interface and satisfaction**	There are 7 items under this domain. A total mean score equal to, or more than, 28 indicates that the app has a good interface and is satisfactory, and vice versa.
**(c) Usefulness**	There are 6 items under this domain. A total mean score equal to, or more than, 24 indicates that the app is useful and serves its purpose and vice versa.

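### A total mean at the exact midpoint of the M-MAUQ scale (72) is labelled good usability, on the point estimate alone

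*Protocol article*

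**What the plan says.** - **Scoring (Variables and tools).** Each of the 18 items is rated on a "seven-point Likert scale ranging from 1 (strongly disagree) to 7 (strongly agree"). For the total, "The highest possible score is 126, and the lowest is 18". Citing the Malay validation paper, the article says that usability is poor "if the average score is less than 4". It then says that an average total of 72 or more means the app is usable.
- **Verdict (3. Expected Results, Phase III).** "A total mean score equal to, or more than, 72 indicates that the app has good usability and vice versa". Totals "will be calculated and expressed as mean and standard deviation (SD) and tabulated". No interval, margin or test is attached to the verdict.
- **Operational definition (Table 3).** The same rule appears: "A total mean score equal to, or more than, 72 denotes that the app has good usability and vice versa". Favourable labels are also given to the domains at total means of 20 (ease of use, 5 items), 28 (interface and satisfaction, 7 items) and 24 (usefulness, 6 items).
- **Sample size (Sample size calculation).** "The sample-to-item ratio of 5:1 will be used", which with 18 items gives 90. The article adds that similar earlier studies were of comparable size.

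**The concern.** Two things are wrong with the verdict.

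First, the label. A respondent who answers 4 throughout sits halfway between strong disagreement and strong agreement and scores 72. On the article's own account, that score is no longer poor and counts as usable. Nothing in the text supports calling the same score good, yet Expected Results and Table 3 both do so.

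Second, the rule reads the sample mean as if it were the true mean. A mean just above 72 and one far above it receive the same verdict, and nothing in the plan says how far above 72 the mean must lie before the difference is more than sampling error.

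This verdict is the main quantitative conclusion of Phase III. The article expects the findings to guide changes before the final prototype, and a public launch with the Ministry of Health and other stakeholders to follow. Those readers would take good to mean more than a midpoint score.

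**Working it through.** **Inputs from the protocol article.** 18 items scored 1 to 7; total 18 to 126; cut-off 72; domain cut-offs 20, 28 and 24; n = 90. **Assumed, because the article gives no SD:** SD of the total score 15, 20 or 25 points (0.83, 1.11 or 1.39 per item after dividing by 18).

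**1. The plan's own figures.** Sample size: 18 × 5 = 90, as stated. Midpoint of the total: (18 + 126)/2 = 72 = 18 × 4, which equals the cut-off. Domain cut-offs: 20/5 = 28/7 = 24/6 = 4, so each is also a midpoint.

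**2. The label at that value.**

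| Place | Item average below 4 | Total mean of 72 or more |
|---|---|---|
| Variables and tools | poor | usable |
| Expected Results, Phase III | not good | good |
| Table 3 | not good | good |

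The number is the same throughout; only the adjective changes.

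**3. Precision at n = 90.** SE = SD/√90. Half-width of the 95% interval = t(0.975; 89) × SE, with t = 1.987. Hence half-width/SD = 1.987/√90 = 0.21.

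**4. Chance of a good verdict when the true mean is 70.** P(observed mean ≥ 72) = 1 − Φ((72 − 70)/SE).

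**5. A lower-limit criterion.** The lower 95% limit reaches 72 when the observed mean is at least 72 + half-width. With a true mean of 75, the chance is about 1 − Φ((half-width − 3)/SE). With a true mean of 70, it is about 1 − Φ((half-width + 2)/SE).

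| Quantity | SD 15 | SD 20 | SD 25 |
|---|---|---|---|
| SE | 1.58 | 2.11 | 2.64 |
| 95% half-width (points) | 3.14 | 4.19 | 5.24 |
| Called good under the stated rule, true mean 70 | 10% | 17% | 22% |
| Observed mean needed for lower limit ≥ 72 | 75.1 | 76.2 | 77.2 |
| Lower limit ≥ 72, true mean 70 | 0.1% | 0.2% | 0.3% |
| Lower limit ≥ 72, true mean 75 | 46% | 29% | 20% |

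**6. Sensitivity to the assumed SD.** With a wider range for the total-score SD, 9 to 36 points (0.5 to 2.0 per item), the chance of a good verdict at a true mean of 70 runs from about 2% (SE 0.95) to 30% (SE 3.79).

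**7. A clearly favourable app.** With a true item mean of 5 (total 90), the lower limit clears 72 with probability above 99%, even at an SD of 36.

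**The case against.** **The study is descriptive.** The objective is to determine usability; there is no hypothesis, comparator or alpha. A reader can compute the interval from the mean, the SD and n, and interval reporting is often left to a fuller document. This is fair as far as reporting goes. It does not cover the verdict, which is fixed in two places on the bare mean; an interval printed beside it would not change when good is declared.

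**The cut-off has a cited source, and higher averages are said to be better.** This also stands: 72 is not arbitrary. What the article reports from that source is the boundary of poor, not of good. Whether the source says more cannot be checked here. That a midpoint score is neutral is inferred from the agree/disagree anchors; the article does not use the word.

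**A lower-limit criterion is strict.** It would miss an app with a true mean of 75 more often than not (met only 20% to 46% of the time), and it still tests against the same midpoint. That is a real cost. It argues for an inconclusive category and a change of label, rather than for a bare pass or fail on the lower limit.

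**Stronger readings that the document does not support.**
- *An app at exactly 72 has an even chance of being called good.* That holds for essentially any cut-off on a sample mean, at any n, and under the stated rule a true mean of 72 already qualifies. It says nothing particular about this plan.
- *The 5:1 ratio is the wrong kind of rule for this study.* The article does not say what the ratio is meant for, and its source is not at hand. All that can be said is that no SD, precision, alpha or power enters the calculation.
- *Ninety is too few.* Nothing shows this; step 7 suggests it is ample if caregivers rate the app well above the midpoint.

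**Conclusion.** The point holds in a limited form. The total and domain cut-offs are exact scale midpoints, and Expected Results and Table 3 attach to the total cut-off a stronger label than Variables and tools supports. This follows from the text and simple arithmetic and needs no assumption.

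The verdict also ignores sampling error. The size of that problem depends on an SD that the article does not give. For a total SD of 15 to 25, the mean is known to within about 3.1 to 5.2 points, and an app whose true mean is 2 points under the cut-off is called good about 10% to 22% of the time (2% to 30% for an SD of 9 to 36). Two points in the total is 2/18 = 0.11 per item, so these are errors close to the boundary. If the observed mean falls far above 72, the conclusion will not change. The calculations treat the sample mean as approximately normal and the 90 responses as independent. They do not address selection bias, which the article acknowledges separately.

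The change should be made: it is cheap and alters what the study can claim. The sample size itself need not change.

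**What to change.** 1. Report the total and the three domain means with 95% confidence intervals, beside the cut-offs 72, 20, 28 and 24.
2. Use one label throughout. For means at or just above 72, apply the wording already in Variables and tools (usable, or not poor) and drop good from Expected Results and Table 3. Moderate the domain labels in the same way.
3. State that usability is shown to exceed a cut-off only when the lower 95% limit is at or above it. When the interval includes values on both sides, call the result inconclusive relative to the cut-off.
4. Keep n = 90 and add its expected precision to the sample size section: a 95% half-width of about 0.21 SD, or roughly 3 to 5 points if the total SD is 15 to 25, with the SD marked as an assumption.

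**Cost.** Some rewording and an extra column in the results table; no further participants. The price is a harder firm claim: an observed mean of about 75 to 77 (4.2 to 4.3 per item) is needed, and an app with a true mean of 75 would reach it only about 20% to 46% of the time.
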